**Evaluations on day -1**

On the day **before** the first dose of BKM120 is given

- Physical examination including height and weight.
- ECOG performance status.
- Patient self-rating mood scales for depression (PHQ-9) and anxiety (GAD-7).
- Vital signs: systolic / diastolic blood pressure (BP), pulse rate.
- Evaluation of toxicity (NCI CTCAE v 4.0).
- Patients will undergo F-Miso PET-CT and perfusion CT scans.
- Blood samples from F-Miso PET-CT.
- Pregnancy test: serum or urine Human Chorionic Gonadotropin (HCG) test to rule out pregnancy at study entry; results must be obtained and reviewed before the first dose of BKM120 is administered.
- Patients will be supplied with BKM120 and will commence treatment on day 1.

**Evaluations from day 8 – 28**

Patients will undergo evaluations on an approximately weekly basis whilst receiving BKM120 (at days 8, 15, 22, 28).

- Haematology – Hb, white blood cells (WBC) with differential count (neutrophils and lymphocytes), platelets and INR.
- Biochemistry – sodium, potassium, calcium, magnesium, phosphate, urea, creatinine, albumin, bilirubin, alkaline phosphatase (alk phos), AST, ALT and LDH. Lipase (days 15 and 28 only).
- FPG.
- Urinalysis (Blood, White Cells, Protein and Nitrites) &/or dipstick for proteinuria (days 15 and 28 only).
- Electrocardiogram (ECG) (days 15 and 28 only).
- Research blood sample for PBMC pAkt level.
- Physical examination including weight.
- Concomitant medications.
- ECOG performance status.
- Patient self-rating mood scales for depression (PHQ-9) and anxiety (GAD-7).
- Vital signs: systolic / diastolic blood pressure (BP), pulse rate.
- Evaluation of toxicity (NCI CTCAE v 4.0).
- Patients will complete treatment on day 37.

On **day 22** patients will also:

- Undergo F-Miso PET-CT and perfusion CT scans.
- Blood samples from F-Miso PET-CT.
- Commence radiotherapy treatment after the imaging investigations have been completed.

**Evaluations on day 42**

Two weeks after completion of treatment, patients will undergo:

- Haematology – Hb, white blood cells (WBC) with differential count (neutrophils and lymphocytes), platelets and INR.
- Biochemistry – sodium, potassium, calcium, magnesium, phosphate, urea, creatinine, albumin, bilirubin, alkaline phosphatase (alk phos), AST, ALT and LDH.
- FPG.
- Research blood sample for PBMC pAkt level.
- Physical examination including weight.
- Concomitant medications.
- ECOG performance status.
- Patient self-rating mood scales for depression (PHQ-9) and anxiety (GAD-7).
- Vital signs: systolic / diastolic blood pressure (BP), pulse rate.
- Evaluation of toxicity (NCI CTCAE v 4.0).

**Evaluations on day 70**

Six weeks after completion of treatment, patients will undergo:

- Haematology – Hb, white blood cells (WBC) with differential count (neutrophils and lymphocytes), platelets and INR.
- Biochemistry – sodium, potassium, calcium, magnesium, phosphate, urea, creatinine, albumin, bilirubin, alkaline phosphatase (alk phos), AST, ALT, LDH and lipase.

- FPG.
- Urinalysis (Blood, White Cells, Protein and Nitrites) &/or dipstick for proteinuria.
- Electrocardiogram (ECG).
- Research blood sample for PBMC pAkt level.
- Physical examination including weight.
- Concomitant medications.
- ECOG performance status.
- Patient self-rating mood scales for depression (PHQ-9) and anxiety (GAD-7).
- Vital signs: systolic / diastolic blood pressure (BP), pulse rate.
- Evaluation of toxicity (NCI CTCAE v 4.0).

## 5.5 End of study evaluations

The end of study visit will occur six weeks after completion of treatment and will involve assessments as described in Sections 5.3 and 5.4.

## 5.6 Evaluations on early withdrawal

Where possible, patients who withdraw early from the study will be evaluated as described in the 'End of study evaluations' section above.

# 6 EARLY PATIENT WITHDRAWAL

## Treatment Withdrawal

During the course of the trial, a patient may withdraw early from treatment. This may happen for a number of reasons, including:

Unacceptable toxicity  
 AE/SAEs requiring discontinuation  
 Clinical decision  
 Patient decision

When the patient stops treatment early, the End of Study Form needs to be completed, along with any other relevant CRFs (e.g. a SAE Form). The reason for withdrawing early from treatment should be clearly documented in the medical records.

## Consent Withdrawal

Consent withdrawal means that a patient has expressed a wish to withdraw from the study altogether. Under these circumstances, the site needs to document all relevant discussions in the patient notes and notify the Trials Office, which will allow the office to mark all future CRFs as not applicable.

Under these conditions, investigators are still responsible to follow up any SAEs till resolution.

## 6.1 Patient evaluability and replacement

### Dose escalation

The MTD will be based on DLTs observed within 6 weeks of completion of BKM120 treatment. DLTs will be assessed whilst the patient is on treatment and for up to 6 weeks after completion of treatment in all patients. Patients completing 14 days of BKM120 treatment who either complete the follow up period or withdraw early ~~from~~ experiencing DLT will be evaluable for dose escalation decisions. Patients who withdraw early for reasons other than experiencing DLT (e.g. progression) will be considered non-evaluable for dose escalation and replaced as necessary to complete each cohort. Patients replaced for dose escalation earlier than the 14 days will be followed up and considered evaluable for toxicity analysis.

### Expansion cohort and cohort 4

Secondary endpoints of changes in F-Misonidazole and in blood flow will be based on F-Miso PET-CT and perfusion CT scans prior to commencing BKM120 treatment and on the day that radiotherapy treatment commences. Patients who have data available from both scans will be considered evaluable for secondary endpoints. Patients withdrawn early or without scans will be considered non-evaluable for secondary endpoints and replaced as necessary to

complete each cohort. All patients who receive at least one dose of BKM120 will be followed up and will be considered evaluable for toxicity analysis.

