| 
 
To determine the safety, dose-limiting toxicity (DLT) and MTD of BKM120 when administered concomitantly with thoracic radiotherapy in patients with incurable NSCLC
 
 | 
Analysis of safety and find the MTD of BKM120. DLTs will be defined per NCI CTCAE v 4.0. The following will be considered DLT if they occur at any point whilst the patient is on study:
 
 
Any <math>\geq</math> grade 3 non-haematological toxicity (excluding nausea, vomiting or diarrhoea) that requires hospital admission or which does not resolve to <math>\leq</math> grade 2 within 7 consecutive days of optimal treatment.
 
Any <math>\geq</math> grade 3 nausea, vomiting or diarrhoea will be considered DLT only if any of them persist for <math>>48</math> hours despite maximum supportive care.
 
<math>\geq</math> Grade 3 pneumonitis
 
Any <math>\geq</math> grade 4 haematological toxicity.
 
Mood deterioration from baseline. DLT will be any grade <math>\geq 3</math> mood change if BL score of 2. DLT will be any grade <math>\geq 2</math> mood change if BL score of <math>\leq 1</math>. The maximum tolerated dose (MTD) is defined as the highest dose at which no more than 1 of 6 evaluable patients or 0 of 3 evaluable patients experience a DLT (see section 6.1).
 
 |

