#### 8.4 Dose modification

If a patient is unable to tolerate BKM120 due to side-effects, then BKM120 will be stopped. Scheduled visits and all assessments should continue to occur except the dosing of BKM120. The BKM120 dose will not be reduced. For replacement of non-evaluable patients see Section 6.1.

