### **17.1 Inclusion in analysis**

All patients enrolled in the study, will be accounted for and included in the analyses. Patients who have completed 56 days on trial or experience a DLT will be included in the dose escalation analysis. The number of patients who were not evaluable, who died or withdrew before treatment began will be recorded. The distribution of follow-up time will be described and the number of patients lost to follow-up will be given.

Variables will be analysed to determine whether the criteria for the study conduct are met. This will include a description of patients who did not meet all the eligibility criteria, an assessment of protocol violations, study drug accountability and other data that impact on the general conduct of the study.

Baseline characteristics will be summarised for all patients who commence BKM120. Patients who do not commence BKM120 or do not complete the required safety observations will be described separately.

Patients will be evaluable for safety and tolerability analysis from the time of their first treatment with BKM120 using NCIC CTCAE v 4.0 scoring and MedDRA coding. Treatment related toxicity will be tabulated by type and grade of toxicity.

Adverse events will be summarised by the number of patients experiencing each type of event. The grades and causality will be reported.

The functional imaging investigations will be used to assess whether BKM120 induces changes in tumour hypoxia and perfusion and to determine whether to open cohort 4. The criteria on which this decision will be based is summarised in Section 12.1.

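### Sections 6.1 and 17.1 define the evaluable set for the DLT/MTD endpoint differently, and 6.1 leaves a DLT that stops drug before day 14 unclassified

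*Protocol*

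**What the plan says.** Section 3 defines the MTD as the highest dose at which "no more than 1 of 6 evaluable patients or 0 of 3 evaluable patients experience a DLT", and refers the reader to Section 6.1. The definition of evaluable therefore sets both the numerator and the denominator of the primary endpoint.

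Section 6.1 (dose escalation) makes evaluable "Patients completing 14 days of BKM120 treatment who either complete the follow up period or withdraw early"; the sentence goes on to give a DLT as the reason for that withdrawal. It continues: "Patients who withdraw early for reasons other than experiencing DLT (e.g. progression) will be considered non-evaluable for dose escalation and replaced as necessary". It then adds: "Patients replaced for dose escalation earlier than the 14 days will be followed up and considered evaluable for toxicity analysis". The same paragraph says "DLTs will be assessed whilst the patient is on treatment and for up to 6 weeks after completion of treatment in all patients".

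Section 17.1 gives the other rule: "Patients who have completed 56 days on trial or experience a DLT will be included in the dose escalation analysis". It sets no minimum exposure.

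Two further sections bear on who falls between these rules:

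- Section 8.4: "If a patient is unable to tolerate BKM120 due to side-effects, then BKM120 will be stopped". The dose is not reduced, and visits and assessments continue without drug.
- Section 8.3: grade 3 pneumonitis is a DLT that ends BKM120. Grade 3 hyperglycaemia stops the drug at once but becomes a DLT only if it lasts more than 7 days despite treatment. During escalation, grade 3 bilirubin or transaminase events worked in the same way.

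**The concern.** In the 6.1 sentence, 14 completed days is the condition and the DLT clause sits inside it. A course in cohorts 1 to 3 lasts only 14 days, so a DLT that ends treatment early fails the condition. The next sentence does not catch this patient either, because it covers only withdrawals for reasons other than a DLT. Section 17.1 includes the patient.

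The rules also part for a patient who stops drug early for toxicity short of a DLT. Section 6 lists unacceptable toxicity among the reasons for early withdrawal from treatment, so 6.1 replaces this patient. Because 8.4 keeps the visits going, the same patient can reach day 56 and count as DLT-free under 17.1, however few doses were taken.

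Finally, 6.1 does not say whether a DLT established only after the drug was stopped still counts, as can happen with hyperglycaemia.

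Each dose level rests on 3 or 6 patients, so one reclassified patient can change the decision. The expansion cohort and cohort 4 are dosed at the MTD that results.

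**Working it through.** **The plan's own count.** Section 16.1 gives a maximum of 18 evaluable patients in escalation: 6 per level x 3 levels = 18. This reproduces, and nothing below changes it.

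**How single patients are classified**

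| Patient | Section 6.1, literal | Section 17.1 |
|---|---|---|
| DLT stops drug before day 14 | outside the evaluable definition, but not named as non-evaluable | included, DLT |
| Stops early for toxicity short of a DLT, seen to day 56 | non-evaluable, replaced | included, no DLT |
| As above, then meets a DLT criterion after stopping | not stated | included, DLT |

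Example: three patients enter a level and one has a DLT on day 10 that stops drug. Under 17.1 the count is 1 of 3 and the level expands to 6. If 6.1 is taken literally, the patient is replaced, and the replacement has no DLT, the count is 0 of 3 and the dose escalates.

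**Chance that a level passes.** From the Section 8.1 table, a level passes with 0/3 DLTs, or with 1/3 followed by 0/3. With true DLT rate p:

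pass(p) = (1-p)^3 + 3p(1-p)^5

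At p = 0.30: 0.343 + 0.9 x 0.168 = 0.494. At p = 0.40: 0.216 + 1.2 x 0.0778 = 0.309.

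**Early DLTs dropped and replaced.** Let f be the share of DLTs that stop drug before day 14. The counted rate is p(1-f)/(1-pf). The protocol gives neither p nor f; both are assumed.

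| p | f | Counted rate | pass, all DLTs counted | pass, early DLTs dropped |
|---|---|---|---|---|
| 0.30 | 0.25 | 0.243 | 0.494 | 0.614 |
| 0.30 | 0.50 | 0.176 | 0.494 | 0.759 |
| 0.30 | 0.75 | 0.097 | 0.494 | 0.911 |
| 0.40 | 0.25 | 0.333 | 0.309 | 0.428 |
| 0.40 | 0.50 | 0.250 | 0.309 | 0.600 |
| 0.40 | 0.75 | 0.143 | 0.309 | 0.828 |

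For instance, 0.30 x 0.50 / (1 - 0.15) = 0.176.

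**Stops short of a DLT replaced.** Let q be the rate of such stops (assumed) and h the share of them who later meet a DLT criterion. Section 17.1 counts the rate p + qh. Replacement under 6.1 gives p/(1-q).

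- h = 0, p = 0.30: pass falls from 0.494 under 17.1 to 0.428 (q = 0.1, counted rate 0.333) or 0.351 (q = 0.2, counted rate 0.375). Replacement exchanges a known zero for a new patient at risk.
- p = 0.20, q = 0.20: 6.1 gives 0.20/0.80 = 0.25, pass 0.600. Under 17.1, h = 0.25 gives 0.20 + 0.05 = 0.25, also 0.600. With h = 0.50 it gives 0.30, pass 0.494, so 6.1 is then the more lenient rule.
- The two rules are equal where p + qh = p/(1-q), that is, h = p/(1-q). The direction turns on how many stoppers later meet a DLT criterion, which the protocol does not give.

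**The case against.** The strongest reply is that 6.1 was meant to count early DLTs. Its replacement sentence reaches only withdrawals for other reasons, and it says that DLTs are assessed in all patients. The synopsis and Section 3 count a DLT at any point while the patient is on study. The Section 8.1 table counts DLTs among the patients entered. Section 8.3 itself treats pneumonitis that ends BKM120 as a DLT. Section 16.1 considers stopping recruitment once 2 DLTs are seen. This stands. A reader might infer from the 6.1 wording that early DLTs were or would be discarded, and the documents do not support that. What remains is that the operative sentence does not say what was probably meant.

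Second, Section 3 points to 6.1 for the MTD and 8.4 points there for replacement, so 6.1 may govern live decisions while 17.1 only describes an analysis set. That is plausible, but neither section says so, and the reported table could then rest on different patients from the decisions that it is meant to document.

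Third, a reader might infer that replacing patients who stop for toxicity short of a DLT also pushes the MTD upward. Against 17.1 it does the opposite unless enough of them later meet a DLT criterion. Without such later DLTs, an upward shift appears only against a rule that counts these stops as events, and no section contains such a rule.

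Fourth, Section 8.3 (liver) says that the escalation phase is complete, so new wording cannot change past decisions. This is right, and it moves much of the remedy to reporting.

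**Conclusion.** The conflict is real and concerns the primary endpoint: 6.1 requires 14 completed days of BKM120, while 17.1 requires either a DLT or 56 days on trial at any exposure. Both rules stand in the protocol, so the conflict is not a detail left to the SAP.

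If 6.1 were applied as written and early DLTs were replaced, the bias could only be upward. At an assumed 30% DLT rate the pass probability moves from 0.49 to between 0.61 and 0.91, and at 40% from 0.31 to between 0.43 and 0.83, for assumed early shares of 25% to 75%. The direction is firm. The size rests on rates that the protocol does not give, and on a literal reading that was probably not intended.

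Replacing patients who stop for toxicity short of a DLT is informative replacement of uncertain direction. It does not support a claim of upward bias.

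**What to change.** Put one definition in both 6.1 and 17.1:

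- A patient with a DLT in the window is evaluable whatever the exposure, including a DLT established after BKM120 was stopped.
- A patient without a DLT is evaluable only with one stated exposure requirement, identical in both sections, plus the full 6-week follow-up.

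Because escalation is complete, the report should also:

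- state which rule governed each escalation decision;
- list every replaced patient with dose level, doses taken and reason;
- show the DLT table by dose level under both the 6.1 and the 17.1 sets.

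The cost is a wording change in two sections, a listing and one extra table. The reported DLT rate may turn out less favourable. The maximum of 18 evaluable patients is unaffected.

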## 7 SAMPLES FOR LABORATORY ANALYSIS

### 7.1 Samples to be analysed in local Trust's laboratories

#### *Diagnostic Laboratories*

Samples for haematology and biochemistry analysis will be labelled with standard patient identifiers and sent to the local hospital diagnostic laboratory. Results will be processed in the standard way and entered into the routine hospital reporting system. Samples will be stored, held reported and subsequently destroyed in accordance with standard local laboratory practice.

### 7.2 Samples to be sent to and analysed in a Central Laboratory

Research blood samples will be collected, processed and stored by the clinical study site in accordance with written instructions that will be provided in a separate sample handling manual. For phospho-Akt expression 20ml blood samples will be taken at the timepoints indicated in Sections 5.3 and 5.4. Samples will be retained and dispatched to a central laboratory for analysis.

The Chief Investigator or designee will apply for access to archival pathology material from the relevant Pathology Department. Any available specimens will be sent to a designated laboratory for central analysis. Separate shipping instructions will be provided.

### 7.3 Summary of research samples to be taken during the study

Assay/sample handling and storage will be managed according to separate written instructions in the Sample Handling Manual. Research assays will be performed according to separate laboratory SOPs.

### 7.4 Pharmacodynamic assays

The levels of phospho-Akt expression in normal tissues may reflect the efficacy of BKM120. Changes in phospho-Akt expression will be monitored during the trial using PBMCs taken at the timepoints indicated in Sections 5.3 and 5.4. Reductions in phospho-Akt expression of PBMC's following BKM120 treatment will be correlated with changes observed with the functional imaging investigations.

### 7.5 Molecular studies

Exploratory studies will aim to correlate response to BKM120 with activation of specific molecular pathways present in the archived, diagnostic, tumour biopsy sample. In cases where there is sufficient tumour tissue available, we will assess pAkt and PTEN levels and then the mutation status of RAS, PI3K and EGFR by PCR. In cases where there is insufficient tissue available to perform these investigations we will prioritise the assessment of pAkt levels.

### 7.6 Labelling and confidentiality of samples sent to central laboratories

All samples sent to analytical Laboratories will be labelled with the trial code, trial patient number, dosing cohort and date taken. Should a laboratory receive any samples carrying unique patient identifiers the recipient must immediately obliterate this information and re-label. The study site will be informed of their error.

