| Blood test for pAkt measurement                                            | X                |        |                         | X                    | X      | X      | X      |
| Coagulation (INR)                                                          | X                |        |                         | X                    | X      | X      | X      |
| Urinalysis                                                                 | X                |        |                         |                      | X      |        | X      |
| Dispensing of BKM120                                                       |                  | X      |                         |                      |        |        |        |
| BKM120 a                                                        |                  |        | Once daily              |                      |        |        |        |
| Radiotherapy                                                               |                  |        |                         | 20 Gy in 5 fractions |        |        |        |
| Pregnancy test (if applicable)                                             |                  | X      | If clinically indicated |                      |        |        |        |

aBKM120 taken at 50mg, 80mg, 100mg (cohorts 1-3 respectively) or MTD (expansion cohort) once daily continuously on days 1-14

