## 2 TRIAL DESIGN

This study will be a single-centre, open-label, 3+3 cohort, dose escalation phase I study of the use of BKM120 in combination with thoracic radiotherapy. Patients with incurable NSCLC requiring palliative thoracic radiotherapy will be eligible for entry. Potential patients will be initially screened to determine eligibility for the main study. For the main study, the first three cohorts of patients will be treated with escalating doses of BKM120. These patients will be treated with BKM120 for a total of fourteen days. One week after commencing BKM120, patients will start palliative radiotherapy treatment. Radiotherapy treatment will be delivered as 20Gy in 5 fractions over a one week period. The delay for radiotherapy, compared to not participating in the trial, for cohorts 1-3 and the expansion cohort will only be a few days and the delay for cohort 4 will be approximately 2 weeks. However since the effects of radiotherapy typically take several weeks to show any benefit the delays are unlikely to change the effect of the radiotherapy.

The MTD will be determined as described in Section 8.1. An additional expansion cohort of a further six patients will be treated with BKM120 in combination with radiotherapy at whichever cohort (1-3) corresponds to the MTD.

In the event that no changes are detected in tumour hypoxia or perfusion in cohorts 1-3, an optional group of patients (cohort 4) will be recruited. These patients will receive BKM120 treatment for a total of 28 days. Three weeks after commencing BKM120, this cohort will receive palliative radiotherapy with 20Gy in 5 fractions over a one week period.

The trial will recruit 2-30 evaluable patients presenting with any stage of NSCLC, requiring palliative radiotherapy treatment.

Refer to the schedule of events and flow chart for details of the study visits and procedures.

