#### Dose escalation phase

Between 2 and 18 evaluable patients will be recruited to the dose escalation phase. The aim of this Phase I study is to define the MTD of BKM120 when used in combination with palliative thoracic radiotherapy. The starting dose will be 50mg od. Unless DLT occurs this will be escalated to 80mg od and then 100mg od. There will be no further dose escalation beyond 100mg od. The study uses a standard 3+3 cohort design. Three patients will be entered at each dose level. At minimum, the criteria for dose escalation will be that if, by 6 weeks after the 3rd patient in each cohort has completed treatment there is no DLT, then the study will proceed to the next dose level. There will be a continuous evaluation of safety data, and dose escalation will be reviewed in response to any emerging safety information, with the Chief Investigator reserving the right to prolong the duration between cohorts as appropriate. The first cohort of patients will be given the starting dose of 50mg od, consideration will be given to stopping the recruitment early whether 2 or 3 DLTs are observed – consequently the minimum number of patients recruited is 2. If no DLT is observed, 3 patients will be entered at the next higher dose level. If 1 DLT is observed, an additional 3 patients will be entered at the same dose level. This process will be repeated until MTD is reached. This is the dose level at which no more than 1 of 6 evaluable patients or 0 of 3 evaluable patients experience a DLT. As a result, the maximum number of evaluable patients that could be recruited is 18 (6 evaluable patients by 3 dose levels)

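### The dosing cohort on every sample label leaves the laboratory reading PBMC pAkt unmasked to dose and schedule, for no stated reason

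*Protocol*

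**What the plan says.** Section 7.6 of the protocol states that all samples going to analytical laboratories are "labelled with the trial code, trial patient number, dosing cohort and date taken". The cohort identifies the treatment. The footnote to the schedule of events for cohorts 1-3 and the expansion cohort reads "BKM120 taken at 50mg, 80mg, 100mg (cohorts 1-3 respectively) or MTD (expansion cohort) once daily continuously on days 1-14", and cohort 4 takes the MTD for 28 days.

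Two kinds of material go to a laboratory under this label:

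- **Blood.** Section 7.2 says "For phospho-Akt expression 20ml blood samples will be taken at the timepoints indicated in Sections 5.3 and 5.4". Section 7.4 gives the planned use: "Reductions in phospho-Akt expression of PBMC's following BKM120 treatment will be correlated with changes observed with the functional imaging investigations".
- **Tumour tissue.** Section 7.5 says "we will assess pAkt and PTEN levels", followed by RAS, PI3K and EGFR mutation status by PCR. The aim is to relate response to "activation of specific molecular pathways present in the archived, diagnostic, tumour biopsy sample".

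Section 3 lists these measurements under tertiary and exploratory objectives. Section 2 describes a "single-centre, open-label, 3+3 cohort, dose escalation phase I study", and section 16.3 plans no randomisation. Sections 7.2 to 7.7 do not say why the laboratory needs the cohort, and they do not say that assays are read masked. Sample handling and assay conduct are left to a manual and laboratory SOPs that are not shown.

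**The concern.** On-treatment PBMC pAkt is the trial's pharmacodynamic evidence that the drug reaches its target. A laboratory that knows the dose level or treatment duration may expect more inhibition at a higher dose or after longer exposure. That expectation can enter wherever the assay leaves room for judgement, for example in repeats, exclusions or thresholds.

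The planned analysis is a correlation with imaging change, and this does not remove the risk. Section 1.3 says the imaging is also meant to show at which doses physiological changes appear. If imaging change varies with dose and pAkt readings lean with dose, the correlation can be created or inflated through dose. In a trial of at most 30 evaluable patients, a few shifted readings could alter an exploratory correlation.

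**Working it through.** The protocol states no figure on this point. The check consists of setting sections side by side, plus a count.

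1. **Does the label reveal treatment?** Yes. Cohorts 1, 2 and 3 map one-to-one to 50, 80 and 100 mg od for 14 days (schedule of events, section 8.1). Cohort 4 is the MTD for 28 days. The label therefore shows dose in escalation and schedule if cohort 4 opens.

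2. **Is the cohort needed to link results to dose?** Not on what the protocol says. The patient number is on the label, and section 4.3 has the trial office register each patient to a cohort.

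3. **Which samples can show a treatment effect?** PBMC pAkt is drawn as follows:
   - Cohorts 1-3 and expansion: screening and days 8, 14, 28 and 56, so 5 in all. The screening sample precedes dosing, so 5 − 1 = 4 are on or after treatment.
   - Cohort 4: screening and days 8, 15, 22, 28, 42 and 70, so 7 in all, of which 7 − 1 = 6 are on or after treatment.
   - At the maximum enrolment in section 16.1 (18 escalation, 6 expansion, 6 in cohort 4), that gives (18 + 6) × 4 + 6 × 6 = 96 + 36 = 132 on- or post-treatment samples.

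4. **What about tumour pAkt, PTEN and mutation status?** They come from archived diagnostic tissue. Trial dose cannot change their true values, and PCR mutation calls leave little room for expectation. The concern has force for PBMC pAkt only.

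5. **Would deleting the cohort be enough?** No. Section 16.1 states "Three patients will be entered at each dose level", and the next level opens only after a review 6 weeks after the last patient in the cohort completes radiotherapy (section 8.7). Patient numbers, if issued in order of entry (an assumption), and collection dates therefore track the cohort. Dates also show the order of visits.

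6. **Which results lie outside the concern?** DLT and MTD rest on graded toxicity (sections 6.1 and 8.1). The secondary endpoints and the cohort 4 decision rest on imaging (section 12.1). None uses pAkt.

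**The case against.** A reader might infer that the label breaks a blind. It does not. The trial is open-label and non-randomised, and no section promises masked assays. The accurate statement is that the laboratory is not masked.

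A reader might also infer that every assay is compromised, or that a dose-response comparison is. The documents support neither. The tumour assays use archived diagnostic tissue, and section 7.4 plans a correlation with imaging, with no comparison of pAkt by dose. Nor can one say that the cohort serves no purpose. None is stated, but the handling manual and laboratory SOPs may give one, or may describe masking within the laboratory.

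The strongest objection is timing. Section 8.3, on liver toxicity, indicates that escalation had already finished when its guidance was updated. Patients still to be sampled would all be at the MTD, where dose is constant, and a new label cannot change assays already read. This reduces the benefit but does not remove it. Schedule still differs between the expansion cohort and cohort 4, and the protocol does not say whether stored escalation samples have been assayed. For a pAkt-imaging correlation, masking to visit and imaging response matters as well, and the fix should cover both.

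The endpoints are exploratory, which limits the consequence. Against that, an open-label trial can mask its laboratory readers at almost no cost.

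**Conclusion.** The point holds in a narrow form. Section 7.6 discloses dose and treatment schedule to the laboratory reading on- and post-treatment PBMC pAkt, without a stated reason. This could bias an exploratory readout and its planned correlation with imaging change. The size and direction of any bias cannot be estimated from the protocol.

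The conclusion rests on two assumptions: that the pAkt assay leaves some room for judgement, and that the unseen manual and SOPs do not already mask the reader. It is a cheap improvement of minor severity, not an error in the trial's primary or secondary analysis.

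**What to change.** - In section 7.6 and the sample handling manual, remove the dosing cohort from the label.
- Label samples not yet assayed with the trial code and a coded sample number in place of the patient number and date. The trial office holds the key.
- State that dose, visit and imaging response are linked to pAkt results only after the assay data are locked.
- If the laboratory does need the cohort, say why in section 7.6.
- In the report, say which pAkt samples were assayed under the cohort label and which under a code.

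The cost is a text change in two documents and a code list kept by the trial office. Visits, sample volumes and patient numbers do not change.
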